## Abstract

**Background:**

Periodontitis is a common oral inflammation, which is a risk factor for adverse pregnancy outcomes. Intakes of vitamin D and calcium are inversely associated with occurrence and progression of periodontitis. This study aims to assess the feasibility of a multi-component intervention, including provision of milk powder supplemented with calcium and vitamin D and periodontal therapy (PT), for improving maternal periodontal health and metabolic and inflammatory profiles of low-income Brazilian pregnant women with periodontitis.

**Methods:**

The IMPROVE trial is a feasibility randomised controlled trial (RCT) with a 2 × 2 factorial design with a parallel process evaluation. Pregnant women with periodontitis, aged 18–40 years and with < 20 gestational weeks (*n* = 120) were recruited and randomly allocated into four groups: (1) fortified sachet (vitamin D and calcium) and powdered milk plus PT during pregnancy, (2) placebo sachet and powdered milk plus PT during pregnancy, (3) fortified sachet (vitamin D and calcium) and powdered milk plus PT after delivery and (4) placebo sachet and powdered milk plus PT after delivery. Dentists and participants are blinded to fortification. Acceptability of study design, recruitment strategy, random allocation, data collection procedures, recruitment rate, adherence and attrition rate will be evaluated. Data on serum levels of vitamin D, calcium and inflammatory biomarkers; clinical periodontal measurements; anthropometric measurements; and socio-demographic questionnaires are collected at baseline, third trimester and 6–8 weeks postpartum. Qualitative data are collected using focus group, for analysis of favourable factors and barriers related to study adherence.

**Discussion:**

Oral health and mineral/vitamin supplementation are much overlooked in the public prenatal assistance in Brazil and of scarcity of clinical trials addressing these issues in low and middle-income countries,. To fill this gap the present study was designed to assess the feasibility of a RCT on acceptability of a multi-component intervention combining conventional periodontal treatment and consumption of milk fortified with calcium-vitamin D for improving periodontal conditions and maternal metabolic and inflammation status, among Brazilian low-income pregnant women with periodontitis. Thus, we hope that this relatively low-cost and safe multicomponent intervention can help reduce inflammation, improve maternal periodontal health and metabolic profile and consequently prevent negative gestational outcomes.

**Trial registration:**

NCT, NCT03148483. Registered on May 11, 2017.

## Strengths and limitations of this study

To the best of our knowledge, this is the first feasibility trial to explore the acceptability of a multi-component intervention combining milk powder supplemented with calcium and vitamin D and periodontal therapy in Brazilian pregnant women.This study will contribute to the limited literature on the impact of milk intake, supplementation of calcium and vitamin D and periodontal therapy for improving maternal metabolic and inflammation status and periodontal health.The evaluation process includes qualitative data to support the assessment of barriers and facilitators related to the study feasibility.Follow-up for this study is limited to 6–8 weeks after birth due to study budget and timeframe. Ideally, longer-term follow-up would be preferable to allow for the initial effect of the intervention to be assessed in both mothers and infants.

## Background

Periodontitis is an inflammatory disease defined as a bacterial gum infection causing a breakdown of soft tissue and loss of tooth-supporting bone [1]. If untreated, periodontitis can cause tooth loss potentially resulting in low self-esteem, impaired speech and chewing and reduced ability to eat healthy and nutritious food [2]. Periodontitis is one of the most common oral conditions and is prevalent in both developed and developing countries reaching approximately 20–50% of the global population [3]. Pregnant women, due to hormonal changes, are prone to develop periodontitis or existing periodontitis may worsen with the progression of pregnancy [4]. In Brazil, the prevalence of moderate periodontitis among pregnant women has been estimated to be between 11% and 47% [5–8].

The inflammatory burden induced from periodontitis may have repercussions beyond the oral cavity, leading to low-grade systemic inflammatory status and metabolic disturbances, which can affect the course of gestation [9]. Increased levels of pro-inflammatory mediators such as interleukin-6 (IL-6), C-reactive protein (CRP) and matrix metalloproteinase 9 (MMP-9) have been observed among people with periodontitis [10–12].

Systematic reviews have shown that women with periodontitis are at higher risk of delivering preterm (< 37 weeks gestation) and low-birth-weight (< 2.5 kg) babies, [13–15] both of which are among the leading causes of neonatal deaths [16]. The biological mechanism underlying the link between periodontitis and adverse pregnancy outcomes is not fully known [17]. Periodontitis may cause bacterial translocation through blood circulation or production of inflammatory mediators associated with premature rupture of membranes and onset of delivery [18]. Additionally, it may initiate and propagate a framework for insulin resistance and ultimately the manifestation of gestational diabetes [9]. The vertical transmission of oral pathogenesis is also a concern, as children of mothers with periodontitis are at higher risk of acquiring periodontal pathogens [19].

Randomised controlled trials (RCT) investigating whether non-surgical periodontal therapy (PT) during pregnancy has the potential of reducing miscarriage, preterm birth and low-birth-weight incidence have shown conflicting results [20–23]. However, the majority of the RCTs have found no significant effect [20, 22, 23], probably due to the PT not being intense or early enough to prevent disease progression, suggesting that ongoing periodontal maintenance treatment throughout gestation might be needed [24].

The active form of vitamin D has an important action in relation to regulating calcium and skeletal homeostasis and also acts as an anti-inflammatory and anti-microbial agent that may be beneficial to periodontal health by antibiotic effects on periodontopathogens and inhibition of inflammatory mediators that contribute to the periodontal destruction [25]. Besides vitamin D, calcium has also been associated with lower occurrence of periodontitis, probably by prevention of alveolar bone loss and better natural dentition, i.e. the higher calcium consumption is associated with lower loss of tooth [26].

Calcium and vitamin D co-supplementation have been hypothesised to act in synergy rather than independently [27], since 1,25-dihydroxyvitamin D acts on the small intestine and kidneys to increase absorption of calcium [25]. Previous studies in an adult Danish population have shown that intakes of calcium within recommendations (1000 and 1200 mg/day for men aged 51–70 and > 70 years, respectively, and 1200 mg/d for women aged ≥ 51 years) are associated with lower risk of periodontitis and tooth loss only among those with higher intake of vitamin D (> 6.8 μg/d) [28, 29]. These studies suggest that calcium obtained from dairy sources was associated with benefits for periodontal health. In addition, a non-randomised clinical trial performed among Indian adults found that the group taking vitamin D (250 IU/day) and calcium (500 mg/day) supplementation for 3 months developed better periodontal health (higher bone density and lower gingival bleeding index) than the group that did not take supplementation [30]. However, larger studies are needed to evaluate the effectiveness of this strategy in pregnant women.

In Brazil, the prevalence of vitamin D insufficiency (defined as 25(OH) D levels < 20 ng/mL) in pregnant women ranges from 16.1 to 43% [31, 32]. Moreover, mean calcium consumption among adult Brazilian women is only 476 mg/d [33], which is below the dietary recommendations of 1000 mg/d [34].

Considering the high prevalence of periodontitis and vitamin D insufficiency and low calcium consumption among Brazilian pregnant women, the purpose of this study is to assess the feasibility and acceptability of a multi-component intervention, including provision of milk powder supplemented with calcium and vitamin D and periodontal therapy (PT), for improving maternal periodontal health and metabolic and inflammatory profiles.

### Objectives

The primary and secondary objectives are described in Table 1.

**Table 1 Tab1:** Objectives of the IMPROVE feasibility trial

Primary	Secondary
1. Feasibility of recruitment strategy for local health service and participants	1. Estimates of effect size and variability to enable accurate sample size and power calculations for a definitive RCT
2. Time necessary to recruit participants	2. Identification of any differences across age groups and other socio-demographic factors with regards to attrition rate
3. Acceptability of the study design and random allocation	3. Identification of key barriers and enablers to adoption, and large-scale implementation, of the IMPROVE trial are
4. What the most appropriate inclusion/exclusion criteria are	4. Definition of required for economic analysis and if they can be collected reliably
5. Estimates of compliance, satisfaction, follow- up and attrition rates	5. The capacity of the research team to embed this study into routine practice in the Public Health Centres
	6. To determine the initial effects of the intervention, time and intervention-time interaction on inflammatory biomarkers concentrations and periodontitis status

## Methods/design

### Study design and setting

The IMPROVE trial is a 2 × 2 factorial feasibility RCT with a parallel process evaluation, i.e. the groups are not cross-over [35], conducted among pregnant women with an existing diagnosis of periodontitis. During recruitment, participants are allocated to one of four intervention arms using a permutated block randomisation matrix (Fig. 1). The arms are as follows:Semi-skimmed powdered milk fortified with additional sachet of 500 mg calcium and 500 IU vitamin D and early PT (PT during pregnancy)Semi-skimmed powdered milk fortified with additional sachet of 500 mg calcium and 500 IU vitamin D and late onset PT (PT after delivery)Semi-skimmed powdered milk with placebo sachet and early PTSemi-skimmed powdered milk with placebo sachet and late onset PT

**Fig. 1 Fig1:**
[figure not shown]
SPIRIT flow diagram of the IMPROVE feasibility trial

The 2 × 2 design allows gathering evidence to feed into an adequately powered RCT to test two different hypotheses, so the four arms will enable estimation of the approximated effect that the specific combinations of the intervention components add to improving concentrations of maternal blood metabolic/inflammation markers and periodontal status.

Baseline data was collected up to second trimester (T0), with follow-up at third trimester (T1) and 6–8 weeks postpartum (T2).

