### Participants and eligibility criteria

The study population includes low-risk adult pregnant women, with periodontitis, attending the prenatal care in the Municipal Health Centre of Duque de Caxias, Rio de Janeiro/Brazil. Inclusion and exclusion criteria are described in Table 2.

**Table 2 Tab2:** Inclusion and exclusion criteria for the IMPROVE feasibility trial

Inclusion criteria	Exclusion criteria
1. Aged ≥ 18 years at the time of recruitment	1. Positive diagnosis of HIV/AIDS, syphilis, psychosis, diabetes before pregnancy, thyroid disease, or any disorder causing vitamin D hypersensitivity (e.g. sarcoidosis and other lymphomatous disorders)
2. > 20 weeks gestation at first prenatal visit	2. Lactose intolerance, milk allergy, history of renal stones or family history of renal stone and hyperparathyroidism
3. Positive diagnosis of periodontitis (≥ 1 tooth with at least one site with ≥ 4 mm of clinical attachment loss (CAL) and presence of bleeding on probing)	3. Extensive dental cavity (crowns of several teeth destroyed by caries) and loss of tooth structure or use of fixed dental braces
4. Cognitively and physically able to complete an interview and oral examination and willing to participate, including provision of blood samples.	4. Use of antibiotics or any immune-suppressants or medication known to affect vitamin D/calcium metabolism
	5. Consumption of ≥ 4 servings/day of dairy products or taking vitamin D supplements > 400 IU/day

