### Recruitment

In the first prenatal visit a member of the research team introduced pregnant women to the study and invited those initially interested in taking part to answer a preliminary checklist for eligibility, except for the diagnostic of periodontitis. After this, women were screened for syphilis and HIV, as part of the routine pre-natal care. Those who were preliminarily eligible and tested negative for syphilis and HIV were then invited to book a dental examination. Those who screened positive for periodontitis were provided with an informed consent form and included in the study (Fig. 2).

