### Randomisation, allocation concealment and blinding

To avoid information bias, regarding influence of interviewer by knowledge of group allocation of participants, randomisation took place after baseline assessment. An online randomisation system with a random mixture of permuted block sizes, stratifying participants by current smoking habit (yes vs. no) was provided and concealed by *Sealed Envelope Ltdtm*.

Due to the nature of the intervention (early vs. late PT), complete blinding of the intervention was not possible. However, dentists and participants were blinded to group allocation regarding milk fortification. Outcome assessment is blinded, and the dentist performing the final periodontal examination is not aware of group allocation regarding both placebo or fortified sachet and PT before or after delivery.

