### Interventions

Participants were advised to take two servings of a powdered vitamin D and calcium plus semi-skimmed milk daily during breakfast and afternoon snack or supper to avoid concomitant intake of the prenatal iron supplements routinely prescribed for consumption with hot main meals (e.g. lunch or dinner). Twenty grams (20 g) of powdered semi-skimmed milk (of a commercial brand available in Brazil) is mixed with a sachet (2 g), containing calcium (CAPOLAC 500 mg) [48] and vitamin D_3_ (500 IU), to be reconstituted in 200 mL of potable water for each serving or other preparations (i.e. to consume with kneaded fruits, fruit smoothies, yogurt, porridge, etc.). Sachets with vitamin D/calcium and milk powder were provided monthly to participants in the fortified group during routine prenatal visits.

In the first dental session, a full periodontal examination was repeated to allow comparison with the first examination done during recruitment (screening) and check the agreement between the two dentists. After that, conventional non-surgical PT, consisting of prophylactic dental polishing to remove the sticky bacterial film that forms on the teeth overtime, scaling and root planning, as necessary, was undertaken throughout pregnancy, up to delivery (Fig. 1). The periodontal treatment is carried out at the Municipal Health Centre of Duque de Caxias. The treatment is performed by a qualified and trained dentist who was not involved in the screening procedure and was blind regarding group allocation.

PT started right after the randomisation to ensure early therapy initiation for the relevant treatment arms. The number of treatment sessions depended on the severity of the disease. However, participants were allowed up to five treatment sessions. In each session, participants also received personalised oral hygiene instructions. Standard fluoride toothpaste, without any additional component that could interfere in results, a toothbrush and dental floss were provided to all participants. Monitoring sessions (reassessment of dental conditions) were taken at 2-month interval. If necessary, PT and oral hygiene instructions were repeated.

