### Control group

The control group are the women assigned to the semi-skimmed powdered milk with non-fortified sachet (placebo) with similar colour, flavour, smell and texture as well as before and after dilution than fortified sachet, during pregnancy and late onset PT (after delivery). Late-onset PT starts after postpartum assessment, as part of the routine dental care in the prenatal clinic. This strategy is considered a more acceptable approach in comparison to offering no PT intervention, since the possibility of being assigned to an ‘untreated’ group could limit recruitment and is more ethical.

All participants were informed about the benefits of dairy food intake during pregnancy and given a brochure to take home with general information about healthy diet and oral health hygiene instructions once they entered the study.

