#### Secondary outcome measures

Changes in mean and SD of percentage of sites with bleeding on probing (BOP) and CAL between postpartum and baselineChanges in maternal blood levels of biomarkers of inflammation (CRP, IL-6 and MMP-9)Changes in maternal blood levels of 25(OH) D, glucose, insulin, calcium, parathyroid hormone and lipids (HDL, LDL and triglycerides)Neonatal blood levels of 25(OH) D and calcium

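### Time on sachets before the T1 blood sample is set only by trimester and can vary several-fold, and the stated ANCOVA adjusts only for the outcome's baseline value

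*Protocol article*

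**What the plan says.** The section on study design and setting gives the schedule in one sentence: "Baseline data was collected up to second trimester (T0), with follow-up at third trimester (T1) and 6–8 weeks postpartum (T2"). T2 has a two-week window. T0 and T1 have neither weeks nor a minimum interval between them.

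Other sections fix where sachet use falls:

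- **Start.** Under randomisation, "randomisation took place after baseline assessment", so T0 precedes the first sachet.
- **Supply.** Under interventions, "Sachets with vitamin D/calcium and milk powder were provided monthly to participants in the fortified group during routine prenatal visits".
- **End.** The control group section places the placebo sachet "during pregnancy and late onset PT (after delivery"), and the patient involvement section speaks of consumption up to the end of gestation.

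Maternal blood is drawn at T0, T1 and T2 (biomarkers and measures). T0 is before treatment and T2 is 6-8 weeks after birth, which leaves T1 as the only maternal sample on sachets.

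The gestational limit at entry is given twice, in opposite directions. The abstract has "aged 18–40 years and with < 20 gestational weeks" and Table 2 has "> 20 weeks gestation at first prenatal visit". The recruitment section then puts further steps between first visit and inclusion: "Those who were preliminarily eligible and tested negative for syphilis and HIV were then invited to book a dental examination". No delay is stated.

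The outcomes concerned are secondary: the inflammatory biomarkers, and "Changes in maternal blood levels of 25(OH) D, glucose, insulin, calcium, parathyroid hormone and lipids (HDL, LDL and triglycerides"). The statistical analysis section uses a repeated measures ANOVA with time at three fixed levels, and an ANCOVA of mean change adjusted for baseline values. Secondary objective 1 (Table 1) is to supply effect sizes and variability for the sample size of a definitive trial.

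**The concern.** A T1 value may come from a woman who has taken sachets for a short time or for most of her pregnancy, yet the analysis treats T1 as a single response. If a marker responds gradually, the T1 contrast between fortified and placebo arms averages over different stages of response. Differences in timing between women also go into the residual SD.

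What is at stake is the quality of the effect and SD estimates handed on under secondary objective 1. A planner who does not know how long the women had been exposed cannot tell whether a small 25(OH)D effect means a weak response or a short exposure.

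**Working it through.** The documents state no figure for time on sachets, so there is none to reproduce.

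**Step 1. Range of exposure before T1.**

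Assumptions: third trimester weeks 28-40; second trimester ends at 27 weeks 6 days; earliest entry at week 8; sachets start at T0. Shortest = earliest T1 minus latest T0. Longest = latest T1 minus earliest T0.

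| Reading of entry | Shortest | Longest |
|---|---|---|
| Abstract (below 20 weeks) | 28 − 19.9 = 8.1 | 40 − 8 = 32 |
| Table 2 (above 20 weeks) | 28 − 27.9 = 0.1 | 40 − 20.1 = 19.9 |
| Schedule sentence alone | 28 − 27.9 = 0.1 | 40 − 8 = 32 |

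Entry at week 6 would raise the 32 to 34. Even the narrowest of these ranges in relative terms, the abstract's, is fourfold (32 / 8). If a limit of 20 weeks applies at the first visit and not at entry, each week of delay takes one week off the minimum: a first visit at week 20 and a 4-week delay leaves 28 − 24 = 4 weeks. That delay is an assumption.

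**Step 2. What it could do to 25(OH)D.**

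The documents give no half-life h, so h = 2, 3 and 4 weeks is assumed. Share of plateau after t weeks = 1 − 2^(−t/h).

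| Weeks on sachets | h = 2 | h = 3 | h = 4 |
|---|---|---|---|
| 4 | 75% | 60% | 50% |
| 8 | 94% | 84% | 75% |
| 12 | 98% | 94% | 88% |
| 20 | 100% | 99% | 97% |

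Now average over women, assuming entry spread evenly (weeks 8-20 for the abstract, 20-28 for Table 2) and T1 spread evenly and independently over weeks 28-40:

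| Reading | Mean share of plateau, h = 2, 3, 4 | SD of that share |
|---|---|---|
| Abstract | 0.997, 0.982, 0.956 | 0.007, 0.022, 0.039 |
| Table 2 | 0.920, 0.846, 0.772 | 0.123, 0.154, 0.168 |

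Under the abstract's limit no woman has less than 8 weeks; under Table 2's about 33% do.

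**Step 3. Consequence for planning.**

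Sample size scales with 1/effect². If the definitive trial meant to measure at plateau, using the diluted effect would oversize it by 1/0.997² to 1/0.956², that is 1% to 9% (abstract), or by 1/0.920² to 1/0.772², that is 18% to 68% (Table 2). If that trial has the same timing as this one, the diluted effect is the right input and there is no oversizing.

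The SD is hardly affected by this mechanism. For a plateau effect of 1 SD, the SD in a fortified arm grows by √(1 + s²): √(1 + 0.039²) = 1.0008 at most (abstract), and √(1 + 0.168²) = 1.014 at most (Table 2).

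**Step 4. What a baseline covariate can reach.**

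On the same even spreads, the variance of exposure time is (entry range²)/12 + (T1 range²)/12. Gestational age at randomisation accounts for 12 / (12 + 12) = 50% of it (abstract) or 5.3 / (5.3 + 12) = 31% (Table 2). The rest is T1 timing, which arises after randomisation.

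**The case against.** The strongest reply is that a journal article condenses. The SPIRIT schedule is in Fig. 1, which is not shown, and visit windows in weeks may be there or in the full protocol. This stands: the absence of weeks from the text is not itself an error. It does not alter the analysis section, which names only baseline values as covariates.

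Second, randomisation follows T0, so timing is balanced between arms in expectation, and the primary outcomes (feasibility, recruitment, adherence, attrition) do not depend on it. Both stand. Neonatal 25(OH)D from a heel prick is a further readout after pregnancy-long exposure, although it is not a maternal sample.

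Third, a reader might infer something stronger: that exposure runs from a few weeks to about 20, and that late entrants are sampled before 25(OH)D reaches its plateau. The documents do not support this. That range matches only Table 2's limit, which the abstract contradicts. The schedule sentence alone allows 0 to about 32 weeks, and the abstract's limit gives a minimum of about 8. The plateau statement needs a half-life that the documents do not give. Nor do they say that the other markers drift with gestation.

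Finally, it is tempting to estimate the effect within bands of weeks on sachets, or to plan from women with 8 weeks or more. The objection to this is sound. The bands depend on attendance and T1 timing after randomisation, and 30 women per arm split three ways leaves about 10 per cell. The longer-exposure subset would overstate the effect for a trial with ordinary recruitment timing.

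**Conclusion.** The point holds in a limited form. As the article states it, time on sachets before the only maternal on-treatment sample varies at least fourfold on any reading of the entry limit, and the T1 model takes no account of it. The abstract and Table 2 must be reconciled before any range can be settled.

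The effect is noise and, on the assumed half-life, dilution: slight under the abstract's limit (mean 96-100% of plateau) and more noticeable under Table 2's (77-92%). Inflation of the SD through variable exposure is at most about 1.4% for a 1 SD effect, so it should not be presented as a serious problem. There is no between-arm bias and no consequence for the primary feasibility outcomes.

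All of this assumes weeks 28-40 for the third trimester, sachets starting at T0, a half-life of 2-4 weeks and, for the averages, evenly spread timing. It is a low-cost improvement to secondary analyses and does not call the design into question.

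**What to change.** - Reconcile the gestational limits in the abstract and Table 2, and state at which step (first visit or entry) the limit applies.
- Prespecify gestational age at randomisation as a covariate in the T1 biomarker ANCOVA, alongside the baseline value of the outcome. It is a baseline value already known from eligibility, so adjustment adds no bias. The expected gain in precision is modest, and the covariate does not undo dilution.
- Report the distribution of weeks from randomisation to T1 by arm, descriptively only, next to the effect and SD estimates meant for the definitive trial. The placebo arms also take sachets, so the same interval is defined in every arm.
- Leave a T1 window tied to time since first sachet as a question for the definitive trial. Recruitment here closed in May 2018, so little could be changed in this trial.

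The cost is a few lines of analysis text, one degree of freedom per model and one descriptive table. No extra data are needed if visit dates are recorded.
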